### **Intervention**

In intervention wards, the nurses and consultant physician, if available, will receive training with emphasis on drug safety, inappropriate drugs for older people, drugs with anticholinergic properties, problems related to psychotropic drugs and the adverse effects related to NSAIDs and PPIs. D-class interactions of drugs will be discussed. We will also give information in these educational sessions about evidence-based treatments in this patient group. The training will be organized as an activating discussion session separately for each intervention ward. Cases related to their own residents will be discussed. Two educational sessions per ward will be organized. In addition, nurses responsible for pharmaceuticals will be provided with more intensive training, together with others responsible for drugs, regarding procedures and processes of how to reduce drug use. A list of inappropriate drugs will be provided to all nurses working in intervention wards. In addition, for each intervention ward a nurse responsible for drugs will be appointed. She/he will bring potential drug problems to the consulting physician in assisted living. In institutions, assisted living facilities and nursing homes in Helsinki, physicians act as visiting consultants to whom the nurses take problematic cases. The physician will take the final responsibility to change or to continue the drugs.

The control wards will continue with the usual care processes. The staff in these wards will receive training in drug treatment after the study is over.

### **Outcome measurements**

The research nurses perform their assessments at zero, six and twelve months.

Primary outcome measures are:

· the proportion of persons using inappropriate, anticholinergic or more than two psychotropic drugs (these drugs are presented in Additional file
1: Table S1), and

· the change in the mean number of inappropriate, anticholinergic and psychotropic drugs.

Secondary outcome measures are:

· change in the mean WHO-defined daily dose
[44] of inappropriate, anticholinergic or psychotropic drugs

· the proportion of persons with significant drug-drug interactions according to SFINX
[27]

· the number of drug-related problems
[46]

· change in the mean number of drugs

· change in the proportion of participants having nine or more drugs

· use of health care services and their costs during a 12-month follow-up

· the number of hospitalizations/follow-up time

· the 15D HRQOL measure
[43]

· cognition according to verbal fluency and clock-drawing test
[38-40], and CDR sum of boxes
[37]

· change in neuropsychiatric symptoms or symptoms of delirium according to the RAI instrument
[45], and

· the number of fallers according to the RAI instrument
[45].

### **Statistical analyses**

Required sample size calculation is based upon the change in the proportion of users of inappropriate, anticholinergic or psychotropic drugs. Sample size was calculated as follows: if in the control group 36% use inappropriate drugs, the minimum group difference with the assessment is 20%, type I error 5%, power 80%, which results in 106/group. Because we recruit participants from wards and aim to include as many as possible from those wards, the final sample size may differ slightly from this figure.

In these baseline findings, for the continuous variables, descriptive values will be expressed by means with standard deviations (SD) and medians with range. For the variables with a normal (Gaussian) distribution, statistical comparisons between the groups will be made by using a *t* test. If the variables have a non-normal distribution or ordinal level, statistical comparison between groups will be performed with the Mann Whitney *U* test. Measures with a discrete distribution will be expressed as percentages (%) and analyzed by *X*^2^ or Fischer’s exact test when appropriate.

The results will be analyzed according to intention to treat. For imputation method, ‘the last observation carried forward’ (LOCF) and ‘worst-rank score’ principle will be used. For the most important outcome parameters, estimation of confidence interval (95%) will be used in addition to testing. Since the distributions of health care costs are highly skewed, the differences between means and confidence intervals are estimated using the bootstrap method (bias corrected and accelerated bootstrapping).

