## **Background**

Polypharmacy and use of inappropriate drugs is very common among frail institutionalized residents
[1-3]. Older people living in nursing homes and institutions are administered an average eight to ten medications
[2,4]. Polypharmacy is a challenge for clinicians, because it is associated with a risk of drug-drug interactions and adverse effects
[5]. In institutional settings, polypharmacy has been defined as using more than eight drugs
[6], or ten or more drugs
[7].

Inappropriate medications for older people have been defined in several different ways
[8-11]. The criteria may be explicit, that is, drug- or disease-oriented, implemented to all patients in a similar way, and thus, simple to use
[12]. The criteria may be also implicit, that is, based on clinical judgment; they may include more complicated domains such as effectiveness, drug-drug interactions, lowest cost or duplications. These kinds of criteria are more comprehensive, but also more complicated to use
[12]. The most widely used international explicit criteria have been developed by Beers’ expert panel
[8,9]. Of Finnish elderly residents in institutional care, 36% were on the Beers’ list of inappropriate drugs
[1,13]. This proportion is similar or lower than those found in respective American or Australian studies
[14,15]. Use of inappropriate medications may not increase mortality, but it may result in unnecessary hospitalizations
[16].

The Omnibus Budget Reconciliation Act of 1987 in the USA succeeded in decreasing the use of harmful psychiatric medications among older people
[17]. There have been warnings concerning the use of antipsychotics in patients with dementia, with an increased risk of stroke and mortality
[18,19]. The use of psychotropic drugs is associated with risk of falls
[20]. There is extensive use of psychotropic drugs in Finnish nursing homes, 80% being administered at least one psychotropic drug
[4].

There is also increasing evidence of the adverse effects of drugs with anticholinergic properties. In addition to the traditional side effects such as dryness of mouth, constipation and worsening glaucoma, they have been shown to be associated with cognitive decline
[21,22], and they may increase the risk of hospital admissions

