The aim of this study is to determine whether training nurses in assisted living facilities in Helsinki would reduce the use of inappropriate medications, anticholinergic and psychotropic drugs among the residents in these houses. In addition, we will examine the effect of intervention on quality of life (QOL), cognition, and use and costs of health services of the participating older people.

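### The sample size enters the 36% Beers-list rate for a composite primary outcome, words that composite differently from the outcome list, and leaves the 20% difference undefined

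*Protocol article*

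**What the plan says.** - **Outcome sized** (Methods, Statistical analyses): "Required sample size calculation is based upon the change in the proportion of users of inappropriate, anticholinergic or psychotropic drugs". No threshold is attached to psychotropic drugs.
- **Inputs** (same section): "if in the control group 36% use inappropriate drugs, the minimum group difference with the assessment is 20" per cent, with type I error 5% and power 80%, giving 106 per group. The section does not say whether the 20% is absolute or relative, or in which direction it runs.
- **Primary outcome** (Methods, Outcome measurements): "the proportion of persons using inappropriate, anticholinergic or more than two psychotropic drugs". The abstract uses the same threshold of more than two psychotropics.
- **Source of the 36%** (Background): "Of Finnish elderly residents in institutional care, 36% were on the Beers’ list of inappropriate drugs".
- **Another component** (Background, Finnish nursing homes): "80% being administered at least one psychotropic drug".
- **Aim** (end of Background): to find out whether training "would reduce the use of inappropriate medications, anticholinergic and psychotropic drugs among the residents in these houses". The intended direction is a reduction.

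**The concern.** The primary outcome is a union of three conditions, and the calculation takes its control rate from one of them. Within one population and one set of drug definitions, a union cannot be less common than any of its parts, so 36% is at best a lower bound for the composite.

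The sizing sentence also describes a wider union than the outcome list does: any psychotropic instead of more than two. With 80% of nursing-home residents on at least one psychotropic, 36% cannot be the rate of that wider union in such a population.

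The control rate fixes what the 20% means. A 20-point fall is a relative reduction of 20/36 = 56% from 36%, 20/60 = 33% from 60%, and 20/80 = 25% from 80%. If the 20% is itself relative, the control rate drives the required number directly. As written, a reader cannot tell which effect on the primary outcome 106 per group was meant to detect.

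**Working it through.** **Inputs.** From Statistical analyses: control rate 0.36, difference 0.20, alpha 0.05, power 0.80. Assumed: two-sided test and 1:1 allocation. The documents give no composite rate, so control rates of 50-90% are an assumed range.

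**Formulas.** With d = |p1 - p2| and pbar = (p1 + p2)/2:

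- n = [1.960·√(2·pbar·(1 - pbar)) + 0.842·√(p1(1 - p1) + p2(1 - p2))]² / d²
- continuity-corrected n = (n/4)·[1 + √(1 + 4/(n·d))]²
- power = Φ{[d·√n - 1.960·√(2·pbar·(1 - pbar))] / √(p1(1 - p1) + p2(1 - p2))}

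**Step 1: reproduce 106.**

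- 36% versus 56%: pbar = 0.46. n = [1.960·√0.4968 + 0.842·√0.4768]²/0.04 = 96.30. Corrected: 106.06, which matches 106.
- 36% versus 16%: pbar = 0.26. n = [1.960·√0.3848 + 0.842·√0.3648]²/0.04 = 74.32, so 75. Corrected: 84.02, so 85. Neither matches.
- 36% versus 28.8% (20% relative): 663, or 690 corrected. No match.
- One-sided, unpooled-variance and arcsine versions of the 20-point comparisons do not give 106 at 80% power either.

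An attrition allowance of 20% on the falling case would give 84.02/0.80 = 105.0, close to 106, but the section states no such allowance. From the stated inputs, only 36% versus 56% reproduces the figure, and that is a rise, against the trial's aim.

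**Step 2: which outcome does 36% fit?**

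| Definition | What the documents imply about its rate |
|---|---|
| Inappropriate (Beers) alone | 36%, institutional care |
| Inappropriate, anticholinergic or any psychotropic (sizing text) | about 80% or more, from nursing-home data |
| Inappropriate, anticholinergic or more than two psychotropics (outcome list) | not below its inappropriate-drug component; no figure given |

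**Step 3: consequence over the assumed range, without clustering.**

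| Control rate | n/arm, 20-point fall (corrected) | Power at 106/arm | n/arm, 20% relative fall | Power at 106/arm |
|---|---|---|---|---|
| 50% | 93 (103) | 84.9% | 388 | 31% |
| 60% | 97 (107) | 83.4% | 270 | 42% |
| 70% | 93 (103) | 84.9% | 186 | 56% |
| 80% | 82 (91) | 89.4% | 123 | 74% |
| 90% | 62 (72) | 95.9% | 74 | 92% |

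Power is from the uncorrected formula. Over whole-percentage control rates from 21% to 99%, the largest requirement for a 20-point fall is 97 (107 corrected).

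**The case against.** The strongest reply is that the planned number survives. The plan claims 80% power, and for an absolute 20-point fall no control rate needs more than 97 per arm, or 107 with correction. The relative reading also fits the plan poorly: at 36% it would need 663 per arm, nowhere near 106, so an absolute difference was probably meant. The abstract and outcome list agree on the threshold, and the sizing sentence may be shorthand like the statement of aim. The endpoint can be identified.

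Most of this stands. It limits the consequence but does not repair the text: 36% is still a component's rate, and an absolute difference still has to be inferred.

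A reader might infer three stronger things that the documents do not support.

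- **That the trial is undersized because of the 36%.** The absolute-difference columns above show otherwise.
- **That 106 against 75 was a reserve for clustering and deaths, which a higher control rate uses up.** The plan claims no reserve. The gap appears only if the calculation is read as 36% to 16%, which does not reproduce 106. Loss of power from randomizing wards is a separate question, and any figure for it needs a ward size and intracluster correlation that the documents do not give.
- **That the listed outcome must be far more common than 36%.** The documents establish only that it cannot be lower than its inappropriate-drug component. They give no rate for anticholinergics or for more than two psychotropics, the drug lists are in an additional file that is not shown, and both Background figures come from institutional care or nursing homes, not assisted living.

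**Conclusion.** The point holds as an error in the basis of the sample size, not as proof of inadequate size. The control rate is that of one component, and the sizing text defines the composite more widely than the outcome list. The stated number follows from the stated inputs only as an increase from 36% to 56%.

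The size of the problem turns on the undefined 20%. As an absolute fall, power at 106 per arm stays at 83-96% for control rates of 50-90%. As a relative fall, it is below the stated 80% at control rates of 50-80% and reaches 92% only at 90%. These figures assume a two-sided 5% test, equal arms, independent residents and no losses; the 50-90% range is an assumption. The matter deserves correction before analysis.

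**What to change.** In Statistical analyses:

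1. Use the primary outcome exactly as listed under Outcome measurements, with more than two psychotropic drugs.
2. Replace 36% with an expected control rate for that composite and give its source. Baseline drug use, pooled over arms, is one option: it is already in the assessment schedule and reveals nothing about the treatment effect.
3. State that the 20% is an absolute reduction, if that is what was meant, and give both proportions.
4. State the formula, the sidedness and any continuity correction, and restate power or the detectable difference at the planned number.

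The cost is a recalculation and a few lines of text, with no new data collection. The downside is that the implied relative effect and the stated power may change once a real composite rate is used.

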****Methods and design**:**

During years 2011 and 2012, a sample of residents in assisted living facilities in Helsinki (approximately 212) will be recruited, having offered to participate in a trial aiming to reduce their harmful drugs. Their wards will be randomized into two arms: one, those in which staff will be trained in two half-day sessions, including case studies to identify inappropriate, anticholinergic and psychotropic drugs among their residents, and two, a control group with usual care procedures and delayed training. The intervention wards will have an appointed nurse who will be responsible for taking care of the medication of the residents on her ward, and taking any problems to the consulting doctor, who will be responsible for the overall care of the patient. The trial will last for twelve months, the assessment time points will be zero, six and twelve months.

The primary outcomes will be the proportion of persons using inappropriate, anticholinergic, or more than two psychotropic drugs, and the change in the mean number of inappropriate, anticholinergic and psychotropic drugs among residents. Secondary endpoints will be, for example, the change in the mean number of drugs, the proportion of residents having significant drug-drug interactions, residents' health-related quality of life (HRQOL) according to the 15D instrument, cognition according to verbal fluency and clock-drawing tests and the use and cost of health services, especially hospitalizations.

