## **Methods**

### **General design**

The study is a randomized controlled trial in which wards in assisted living facilities in Helsinki are randomly allocated to two arms. The staff in intervention wards will receive two half-day training sessions concerning appropriate use of drugs among frail older people. Approximately 212 patients will be included: 100 subjects in the intervention group and 100 in the control group. The number of patients per group may vary, because the wards randomized may vary in size. The study has been approved by the ethics committee of Helsinki University Central Hospital. Informed consent has been obtained from each patient and/or their closest proxy before any study procedure is performed according to good clinical practice.

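### The 106 per group does not follow from the stated inputs for a reduction (36% to 16% needs about 75, or 84–85 with continuity correction); it matches an increase to 56%, and the 100 + 100 split does not sum to 212

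*Protocol article*

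**What the plan says.** Under Statistical analyses, the protocol article bases the sample size on the proportion of users of the target drugs. The inputs are "if in the control group 36% use inappropriate drugs, the minimum group difference with the assessment is 20" per cent, followed by "type I error 5%, power 80%, which results in 106/group". It does not give an intervention-arm proportion, a direction, or whether the 20% is absolute or relative. It mentions no inflation for clustering or losses. The only qualification is that, because recruitment is by ward, "the final sample size may differ slightly from this figure".

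The direction sought is given at the end of the Background: the study asks whether training nurses "would reduce the use of inappropriate medications, anticholinergic and psychotropic drugs among the residents".

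The abstract says that "a sample of residents in assisted living facilities in Helsinki (approximately 212) will be recruited", which equals 2 × 106. General design says "Approximately 212 patients will be included: 100 subjects in the intervention group and 100 in the control group", and adds that group sizes may vary with ward size.

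**The concern.** A sample size statement should let a reader go from its inputs to its result. Here the inputs, taken in the direction the trial intends, lead to a clearly smaller number than the one stated. The stated 80% power is therefore not the power that 106 per group gives for a 20-point reduction. Anyone judging a null result, or asking how much reserve there is for ward randomization and deaths, would start from a wrong figure. The planned split of 100 and 100 adds a second inconsistency, because it does not sum to the total in the same sentence.

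**Working it through.** **Inputs.** Control proportion 36%, difference 20%, type I error 5% and power 80% come from Statistical analyses. The direction (reduction) comes from the Background. Equal allocation follows from the single per-group figure. Two assumptions are mine: the 20% is absolute percentage points, and the test is two-sided (z = 1.960 and 0.842).

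**Formulas.** With p̄ the mean of the two proportions and d their difference:

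- Uncorrected: n = [1.960·√(2p̄(1−p̄)) + 0.842·√(p₁(1−p₁) + p₂(1−p₂))]² / d²
- Continuity-corrected: n′ = (n/4)·[1 + √(1 + 4/(n·d))]²

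**Reproducing 106: 36% against 56%.** Here p̄ = 0.46.

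- n = [1.960·√0.4968 + 0.842·√0.4768]² / 0.04 = (1.381 + 0.581)² / 0.04 = 96.3
- n′ = (96.3/4)·[1 + √(1 + 4/19.26)]² = 106.06

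This matches 106 to the nearest whole number, but it describes more use of these drugs in the trained wards.

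**The reduction the trial seeks: 36% against 16%.** Here p̄ = 0.26.

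- n = [1.960·√0.3848 + 0.842·√0.3648]² / 0.04 = (1.216 + 0.508)² / 0.04 = 74.3, so 75 per group (150 in total)
- n′ = (74.3/4)·[1 + √(1 + 4/14.86)]² = 84.02, so 84–85 per group (168–170 in total)

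**Other formulas for the same reduction, at 80% power.**

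| Variant | n per group | With continuity correction |
|---|---|---|
| Two-sided, pooled variance | 75 | 84–85 |
| Two-sided, unpooled variance | 72 | 82 |
| Two-sided, arcsine | 73 | – |
| One-sided, pooled variance | 59 | 69 |

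None is near 106. The stated figure exceeds the requirement by a factor of 106/75 = 1.41, or 106/84 = 1.26 with continuity correction.

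**Power that the planned numbers give (individual level, no clustering, no losses).** For 36% against 16% with 106 per group, the standard normal deviate is (0.20·√106 − 1.216)/0.604 = 1.396, which is 91.9% power.

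| Comparison | n per group | Power | With continuity correction |
|---|---|---|---|
| 36% vs 16% | 106 | 91.9% | 89.1% |
| 36% vs 16% | 100 | 90.3% | 87.1% |
| 36% vs 56% | 106 | 83.7% | 79.9% |

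The stated 80% appears only in the last row, with continuity correction.

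**Split against total.** 106 + 106 = 212, which agrees with the abstract. 100 + 100 = 200, which is 12 short of the total in the same sentence.

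**The case against.** The strongest reply is that the four stated inputs do yield 106 if the difference is added to 36%, and that the paragraph states no direction. With a two-sided test, moving towards 50% is the more demanding case, so 106 covers a 20-point difference either way. This stands. A reader might infer that the stated figures cannot all be true together, and that is too strong. The fault is that they fit together only in the direction opposite to the aim.

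A second reply is that the gap may hide an allowance. A 20% loss allowance on the corrected figure gives 84/0.8 = 105 or 85/0.8 = 106.25, and 36% against 18% with continuity correction gives 105.1. So the origin of 106 cannot be settled from this document. But the text presents 106 as the result of the listed inputs alone, and a reader should not take the surplus for a design-effect or dropout reserve.

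A reader might also take the 20% as relative (36% to 28.8%) and conclude that the trial is grossly underpowered. That reading needs about 663 per group, so the stated 106 itself rules it out.

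On the split, total numbers are described as approximate and wards vary in size. That explains unequal or inexact arms, but not two planned arms that miss their own total. The intended figure is clear from the abstract and from Statistical analyses, so this part is a slip.

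Finally, an article may leave sidedness, formula and loss allowance to the full protocol. That is fair, and their absence is not the complaint. The complaint is a stated result that does not follow from the stated inputs in the intended direction.

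**Conclusion.** The point holds as an error in the written justification. For an absolute 20-point reduction from 36%, with two-sided 5% and 80% power, the requirement is about 75 per group, or 84–85 with continuity correction. The stated 106 corresponds to a 20-point increase with continuity correction.

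The discrepancy is conservative: at individual level the planned 106 per group has about 92% power for the intended effect (about 89% corrected). On this point alone the trial is not short of participants, and no analysis changes. The power figures treat residents as independent and all observed. Wards are randomized and the Discussion expects deaths, so they are not the trial's real power. The documents give nothing from which to compute that.

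**What to change.** In Statistical analyses, restate the calculation with both proportions (36% and 16%) and say that the difference is in absolute percentage points. Then give one of two things:

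- the number these inputs yield: 75 per group, or 84–85 with continuity correction; or
- the individual-level power that 106 per group provides: about 92%, or about 89% with continuity correction.

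In either case, say that the figure ignores ward clustering and losses. Do not describe the surplus up to 106 as a planned design-effect or dropout allowance unless one was actually used. In General design, change the split so that it agrees with the total (106 + 106 = 212).

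The cost is a text correction, with no change to recruitment, design or analysis.

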**Figure 1 F1:**
[figure not shown]
Flow chart.

**Table 1 T1:** Study assessment procedures and timetable

**Assessment**	**Comparability of wards; interview**	**Baseline assessment**	**Six-month assessment**	**Twelve-month assessment**
Inclusion criteria, informed consent	X			
Demographics, diagnoses		X		
CDR		X		
MMSE		X	X	X
Verbal fluency, clock-drawing test		X	X	X
MNA		X		
Drug use		X	X	X
15D QOL measure		X	X	X
PWB scale		X	X	X
RAI assessment	X	X	X	X
Falls			X	X
Hospitalization, use of health and social services, mortality				X
X				

CDR, clinical dementia rating scale (Hughes et al. 1982); MMSE, Mini Mental State Examination (Folstein et al. 1972); MNA, Mini Nutritional Assessment (Guigoz et al. 2002); 15D, health-related quality of life scale (Sintonen et al. 1990); PWB, psychological well-being scale (Routasalo et al. 2009); RAI, Resident Assessment Instrument (Morris et al. 2000).

Drug use will be assessed as the point prevalence on the day of assessment. Residents will be classified as regular drug users if their medical charts indicate a regular sequence of administration on a daily basis. Additional analyses will be performed including both regularly used drugs as well as drugs used on a *pro re nata* (*prn*, or as needed) basis. The drugs administered to residents will be classified according to the anatomical therapeutic chemical (ATC) classification system recommended by the World Health Organization (WHO)
[44]. The drugs that will be considered as inappropriate, having anticholinergic properties or being psychotropic drugs are presented in Additional file
1: Table S1. The total number of these drugs each resident is using one, on a regular daily basis and two, both regularly or *prn* will be counted.

We randomized wards instead of individual participants in order to avoid contamination. The wards selected for this study were all using the Minimum Data Set (MDS)/Resident Assessment Instrument (RAI) version 2.0 for home care

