[45]. MDS is used for assessing the residents’ needs and for individual care planning purposes. Each nurse has been educated to use MDS, and the assessment is routinely performed twice annually or whenever there is a substantial change in the resident’s status. In addition to the internationally well-validated scales and items, MDS provides a patient’s ward profile, often called ‘the case-mix’ (for example, ‘psychogeriatric’, ‘physically disabled’ or ‘cognitively impaired’), and gives the mean level of residents’ need for assistance. After identifying the case-mix in each of the wards, the wards will be divided into dyads having approximately the same characteristics. These dyads will be further randomized, by means of computer-generated random numbers, into two arms: those to receive staff training or to receive education after the trial. In addition, individual RAI items (for example, the proportion of fallers) and some of the well-validated RAI scale items (for example, neuropsychiatric symptoms, symptoms of delirium) will be used in measuring the effects of intervention.

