## **Discussion**

This rigorous randomized trial will test whether a relatively light educational intervention will have an effect on the use of inappropriate, anticholinergic and psychotropic drugs use among frail older residents in assisted living facilities. The drugs considered in this trial include a wide variety of potentially harmful drugs that have been shown in recent years to have adverse effects in this particular patient group. Intervention is pragmatic in nature, and its potential effects rely on those professionals who actually work with these older people. The nurses will be trained to identify the harmful drugs, whereas the final decision to stop these medications will be made by physicians consulting to these wards. Thus, if the intervention proves to be effective, it can be implemented easily.

The strength of this study is its pragmatic nature and easily implemented training. Thus, the findings should be applicable in real life. The population is frail and vulnerable and, according to our previous studies, uses a high number of these drugs. Thus, the floor effect is not easily reached in the primary endpoint. Besides the number of potentially harmful drugs, this study will also examine the effects of intervention on residents’ QOL. Contrary to many previous trials, this study will also collect data on participants’ hospitalizations. Inappropriate drugs according to Beers, anticholinergic drugs, as well as psychotropic drugs have been suggested to increase hospitalizations and complications
[16,19,23,25].

However, there are also potential limitations in this study. First, the population is old and frail with many comorbidities, and, thus, vulnerable to competing causes of complications and deaths. This may decrease the power of the study. The second challenge relates to a sufficient difference to be attained between the groups with our intervention. Contamination might be a problem, because the staff changes rapidly in these institutions and they may also move from intervention site to control site. The staff is also stressed, and it is unclear how they will accept our training. In addition, the staff will also learn about evidence-based treatments in this patient group (such as the beneficial effects of vitamin D, stroke prevention, dementia drugs, pain treatment), which may increase the number of medications, and, thus, may even have effects in the opposite direction from that intended in this study.

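### The stated 80% power comes from a calculation for independent individuals, so it is not shown for a trial that randomises wards in matched dyads

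*Protocol article*

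**What the plan says.** The General design section states that "wards in assisted living facilities in Helsinki are randomly allocated to two arms". The Study procedures text after Table 1 gives the reason, "We randomized wards instead of individual participants in order to avoid contamination", and adds that "the wards will be divided into dyads having approximately the same characteristics" before randomisation.

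The sample size is in Statistical analyses. Its inputs are a control proportion ("if in the control group 36% use inappropriate drugs"), a difference ("the minimum group difference with the assessment is 20" per cent), and the error rates with their result: "type I error 5%, power 80%, which results in 106/group". Wards appear in that paragraph only as a reason why the final number may differ slightly. The planned total of about 212 equals 2 × 106, so nothing was added after the calculation. (General design also splits it as "Approximately 212 patients will be included: 100 subjects in the intervention group and 100 in the control group", which does not add up to 212.)

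On deaths, the Discussion calls the population "vulnerable to competing causes of complications and deaths. This may decrease the power of the study". No allowance is put into figures. Statistical analyses plans intention to treat, with last observation carried forward and a worst-rank score.

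**The concern.** Residents of one ward share a case-mix, the same trained staff, an appointed nurse for drugs and a visiting consultant physician (Intervention section). Their drug use is therefore likely to be correlated. A calculation that treats residents as independent gives the power of a different design.

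The printed 80% is the figure a reader would use to interpret a null result. The Discussion already doubts that a sufficient difference between groups can be reached and names contamination as a risk, so a null result is plausible. If power was in fact well below 80%, such a result could be over-read as evidence that training does not work.

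**Working it through.** **Inputs from the protocol.** Control proportion 36%; difference 20%; type I error 5%; power 80%; 106 per group. Sidedness is not stated, and two-sided is assumed. The difference is read as 20 percentage points. A relative 20% (36% against 28.8%) would need 663 per group, far from 106.

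**Inputs not in the protocol (assumed).** ICC 0.02, 0.05 and 0.10; m = 8, 10 and 15 participating residents per ward, with equal ward sizes.

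**Step 1: reproduce the 106.** With p̄ the mean of the two proportions and d their difference:

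n = [1.96 √(2 p̄(1 − p̄)) + 0.8416 √(p1(1 − p1) + p2(1 − p2))]² / d²

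Continuity correction: n_c = (n/4) [1 + √(1 + 4/(n d))]²

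- 36% against 56%: p̄ = 0.46, n = (1.3815 + 0.5811)² / 0.04 = 96.3, n_c = 106.06. This matches 106.
- 36% against 16%: p̄ = 0.26, n = (1.2158 + 0.5083)² / 0.04 = 74.3, so 75; n_c = 84.02, so 85. Neither matches.

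A contrast of 36% against 18% with correction (105.1, so 106) also matches, but 18% does not stand in the protocol. Both matches have a design effect of 1 and no loss.

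**Step 2: what 106 can absorb in the intended direction.** For 36% against 16%, power with 106 independent residents per group is 92%. It stays at 80% or above up to a design effect of 106/74.3 = 1.43 (106/84.02 = 1.26 with correction). With design effect = 1 + (m − 1) × ICC, the largest tolerable ICC is (1.426 − 1)/9 = 0.047 at m = 10 (0.029 with correction).

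**Step 3: power over the assumed range.** Effective n = 106 / design effect, no loss, normal critical values, no continuity correction:

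power = Φ{[d √n_eff − 1.96 √(2 p̄(1 − p̄))] / √(p1(1 − p1) + p2(1 − p2))}

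36% against 16% (design effect in brackets):

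| ICC | m = 8 | m = 10 | m = 15 |
|---|---|---|---|
| 0.02 | 88% (1.14) | 87% (1.18) | 84% (1.28) |
| 0.05 | 82% (1.35) | 79% (1.45) | 73% (1.70) |
| 0.10 | 73% (1.70) | 68% (1.90) | 57% (2.40) |

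For 36% against 56%, the contrast that reproduces the 106, power at m = 10 is 77%, 68% and 56% for the three ICCs.

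Critical values from a t distribution, with degrees of freedom set by the number of wards, would lower all these figures. The number of wards is not given, so the size of that step is left open.

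**The case against.** The strongest reply is that 106 exceeds what the intended contrast needs under individual randomisation by a factor of 1.43, so a margin may have been built in. At ICC 0.02 power is 84% to 88% across the ward sizes considered, and at ICC 0.05 with 8 per ward it is still 82%. This stands as far as it goes: a reader might infer that the trial's power is below 80%, and the protocol does not support that. It gives no ICC or ward size from which a shortfall could be proved. But the margin is not presented as an allowance for clustering. The 106 is also matched by a formula with a design effect of 1, though that match is inferred from the arithmetic and not stated in the protocol.

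A second tempting step is to take expected deaths straight off the sample size. The planned analysis does not support it: carrying observations forward and assigning worst ranks keep participants in the analysis. Imputation may dilute the effect instead. The Discussion's warning about power is real, but its size cannot be read from the document.

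Third, matching wards in dyads may recover some precision, at a cost in degrees of freedom. The net direction is unknown, and the calculation takes no credit for it.

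Fourth, an article condenses, and a separate analysis plan may say more. That would excuse an omitted detail. Here the article prints the inputs, the result and a total equal to twice that result, so the power claim itself was calculated for another design. The 95% confidence intervals planned for the most important outcomes limit over-reading of a null result, but they do not make the printed power right.

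**Conclusion.** The point holds in this form: 80% power is not shown for the ward-randomised design, because the calculation treats residents as independent and contains no ICC, ward size, number of wards or loss. The size depends on assumptions. For a fall from 36% to 16% without loss, power runs from 88% (ICC 0.02, 8 per ward) to 57% (ICC 0.10, 15 per ward). It falls below 80% once the design effect passes about 1.43, or 1.26 if the continuity correction is kept. For the contrast that reproduces the 106, power at 10 per ward is already 77% at ICC 0.02. The ICCs, equal ward sizes, two-sided test and normal critical values are assumptions, and any effect of matching is left out.

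**What to change.** Replace the 80% claim with the power delivered by the wards and residents actually available. State:

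- that the 20% is in percentage points, if so, and its direction (36% to 16%, or another contrast), and whether a continuity correction is used;
- the number of wards, their mean size and its variation;
- an ICC range such as 0.02 to 0.10, or an ICC estimated from the trial's own baseline drug-use data, with power across it and critical values suited to the number of wards;
- deaths and other loss as a conditional scenario consistent with the planned last-observation and worst-rank handling, which may dilute the effect instead of removing participants;
- any credit taken for matching in dyads, with the assumption behind it.

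The cost is a recalculation and one paragraph. No extra recruitment and no change to the design is asked for. The downside is that the stated power may be less favourable.
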